### Exclusion criteria

2.5

Participants will be ruled out if they meet any criteria below: pregnant or lactation; history of neurologic or psychiatric disorders; participating in such cognitive experiments within 1 year; any other health problems or poor physical conditions that may influence participation; any brain structure damage or abnormalites identified by MRI examinations; any history of alcohol or drug dependency; any MRI contraindications.

### Sample size

2.6

When calculating the sample size during the acupuncture-neuroimaging study, the number in published literature and previous studies is often considered. On the one hand, in fMRI studies, millions of voxels are used to estimate the blood oxygen level dependent (BOLD) signal indirectly, and conventional power calculations often make no sense. On the other hand, the number of participants is often constrained by scanning time and costs. In hence, considering the published acupuncture-neuroimaging literature focusing on sleep disorder, the sample size range of 16 to 32 cases show enough statistical power for brain functional analysis.^[21]^ In the present study, we plan to recruit 60 patients with SWD and 30 healthy subjects with regular sleep.

### Randomization and blinding

2.7

Randomization will be carried out in 2 steps. Firstly, according to the inclusion exclusion criteria, the 90 participants will be divided into experimental group and control group by the ratio of 2:1; secondly, the patient with SWD will be divided into TATG and SATG according to the computer-generated random sequence using Excel's rand function (1:1 ratio). The code will be sealed in opaque envelopes and opened by researchers not involved in the recruitment following informed consent procedures and baseline testing, with direct responsibility for treatment allocation. The researchers and acupuncturists will know the allocation. Meanwhile, the participants, outcome assessors and data analysts will be blinded.

### Patient and public involvement

2.8

Participants in this study will not be involved in the design, recruitment or conduction of the study. After the MRI scanning, all participants will be informed of the results of neuroimaging data in the form of pictures.

## Interventions

3

Patients with SWD will receive true or sham acupuncture treatments for 4 weeks, while healthy subjects will receive no intervention.

### True group acupuncture

3.1

Patients in this group will receive 4-week manual acupuncture treatments at 10 verum acupoints (VA) (bilateral Fengchi (GB20), Benshen (GB15), Shenting (GV24), Shenmen (HT7), and Sanyinjiao (SP6)) with disposable sterile filiform needles (size 0.25 mm × 40 mm, Ande brand, manufactured by Ande Medical Appliance in Guiyang, Guizhou Province, China). Needles will be perpendicularly inserted into acupoints by clamping after skin disinfection using 75% alcohol. The depth of acupoint insertion was 0.5 to 1 inch, needles will be retained at the acupoints for 20 minutes after the deqi sensation is attained through the manipulation of lifting, thrusting and thrusting mild reinforcing-reducing method.

Two acupuncturist with over 5 years of clinical experience in acupuncture will be trained together and conduct the acupuncture treatments. After the first MRI scanning, the participants will receive a total of 8 sessions of acupuncture treatments in 4 weeks.

### Sham acupuncture group

3.2

Patients in sham acupuncture group will receive 4-week manual acupuncture treatments at 10 sham acupoints (SA). According to the previous literature on setting locations of SA,^[22]^ the SA should be set aside with 1 inch beside the true point as the sham acupoint. In hence, the deqi experience of the participants in SATG will not be overemphasized. In spite of the locations of acupoints, the treatment procedures and course will be the same with TATG.

## Measurements

4

The measurements consist of 3 parts including neuroimaging scanning assessments, cognitive function assessments, and needle sensation assessment. The study schedule is shown in Figure 2.

**Figure 2 F2:**
[figure not shown]
Schedule of study. ANT = Attentional Network Test, FC = functional connectivity, PSQI = Pittsburgh Sleep Quality Index scale, REBANS = Repeatable Battery for the Assessment of Neuropsychological Status.

### Demographic and basic clinical information collection

4.1

The demographic information (name, sex, age, height and weight), and the history of other concomitant diseases will be obtained at the baseline. Vital signs (blood pressure, pulse, respiration rate and temperature) will be measured before each scanning.

### MRI scanning and neuroimaging outcomes

4.2

#### MRI scanning protocol

4.2.1

MRI examinations, including resting-state blood oxygenation level-dependent imaging (RS-BOLD fMRI) and high-resolution anatomical T1-weighted imaging (T1W1), are designed for detecting cerebral function changes.

MRI Examination will be acquired applying a 3.0 Tesla MRI scanner (Siemens, Prisma Germany) at Anding Hospital, Beijing, China. Prior to scanning, all participants were asked to rest for 30 minutes before scanning. They were instructed to stay still, think of nothing in particular, keep eyes closed, and not to fall asleep during scanning. Earplugs were worn to attenuate scanner noise. The foam head holders were immobilized to minimize head movements during scanning.

Prior to the functional scanning, we collected high-resolution structural information for anatomical localization by using 3D MRI sequences. The resting-state fMRI data were collected using a single-shot, gradient-recalled echo-planar imaging sequence with the following parameters: repetition time = 2000 ms, echo time = 30 ms, flip angle = 90°, matrix = 64 × 64, field of view = 225 mm × 225 mm, slice thickness = 3.5 mm, gap = 1 mm, 32 interleaved axial slices, and 180 volumes.

#### Neuroimaging outcomes

4.2.2

The neuroimaging outcomes will be acquired after the MRI scanning and analysis, mainly including functional connectivity (FC) within and between resting-state brain networks. FC will be taken as the primary outcome and effect indicator, which is an optimal parameter to reflect the functional connections within and between resting-state brain networks. Numerous studies revealed changes of the brain's intrinsic functional connectivity stemming from cognitive impairments on patients with sleep disorder.^[23,24]^ In hence, FC could reflect whether specific brain regions or resting-state brain networks are involved in improvements of cognitive functions after 4-week acupuncture treatments.

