**Methods and analysis::**

This is a randomized controlled neuroimaging trial, with enrolled participants, outcome assessors, and data statisticians blinded. 60 patients with SWD and 30 healthy controls who sleep regularly will be recruited and divided into divided into a control group, a true acupoints treatment group (TATG) and a sham acupoints treatment group (SATG) by the ratio of 1:1:1. The TATG and SATG will receive 8 sessions of acupuncture treatment in 4 weeks. Cognitive function scales and MRI scanning will be performed before and after 4-week acupuncture treatment. The control group will receive no intervention. Functional connectivity of intra-network and inter-network will be the primary outcome and effect indicator. The secondary outcomes included Repeatable Battery for the Assessment of Neuropsychological Status, Attentional Network Test, Pittsburgh Sleep Quality Index scale and needle sensation assessment scale. Neuroimage indicators will be correlated with clinical data and scores of cognitive function assessment to explore the possible mechanisms underlying the changes of brain activity caused by acupuncture treatment.

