**Discussion::**

The results of this study will enable us to verify the therapeutic effect of acupuncture on SWD and explore the potential central mechanism of acupuncture on SWD from the change of brain activity.

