#### Functional connectivity analysis

5.2.2

Independent component analysis was applied to extract the resting-state brain networks by GIFT software (University of New Mexico, Albuquerque, NM). The number of independent components in all data was calculated by method of the minimum description length (MDL) technique. 30 components were estimated. Randlnit and Bootstrap operations were applied to evaluate the independent components. According to research objectives, independent components were selected based on the largest spatial correlation comparing with previous resting-state brain network templates. Then, resting-state brain networks were calculated by the way of goodness of-fit after removing the components not related to the spectrum of resting-state networks. The best goodness-of-fit score of components were normalized to *Z*-scores with Fisher's *r*-to-*z* transformation to acquire the entire brain *Z*-score map of each subject. Then we extracted time series of each network component to calculate the Pearson correlation coefficient (*r*) of each network component and other network time series, namely functional network connectivity (FNC). The resulting r values were normalized into *Z* values by Fisher-*Z* transformation. For group-level analyses, the functional connectivity of Intra-network and inter-network was performed by one-way ANOVA using SPM12 software (*P < *.05, corrected by false discovery rate (FDR) for multiple comparisons). Finally, BrainNet Viewer was used to display the result onto a 3D brain surface.

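### The primary connectivity test includes non-randomised healthy controls and fixes no time point, true-versus-sham contrast or FDR family, so it can be positive when acupuncture has no specific effect

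*Protocol article*

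**What the plan says.** The abstract (Methods and analysis) states: "Functional connectivity of intra-network and inter-network will be the primary outcome and effect indicator". Section 4.2.2 repeats this: "FC will be taken as the primary outcome and effect indicator". Neither place names a network, a connection, a time point or a direction that counts as improvement.

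Section 5.2.2 sets out the analysis. On the number of components it says: "The number of independent components in all data was calculated by method of the minimum description length (MDL) technique. 30 components were estimated". On selection it says: "independent components were selected based on the largest spatial correlation comparing with previous resting-state brain network templates". Components unrelated to resting-state networks are removed. Intra- and inter-network connectivity is then compared by one-way ANOVA in SPM12 at P < .05 with FDR correction. The section does not say whether the baseline scan, the post-treatment scan or the change is tested. It mentions no pairwise comparison, and it does not say whether the correction covers intra- and inter-network tests together. Two-group follow-up appears only in section 5.1, for clinical data.

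Section 2.1 gives three groups in a 1:1:1 ratio: healthy controls, true acupoints (TATG) and sham acupoints (SATG). Under section 2.7 the first split, patients versus controls, follows the eligibility criteria. Only the second split, TATG versus SATG, is random. RBANS, ANT and PSQI are secondary outcomes. The abstract's discussion says the results will "verify the therapeutic effect of acupuncture on SWD".

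**The concern.** A primary outcome should be one variable, or one defined family, tested by the contrast that answers the trial question. Here that question is true versus sham acupuncture, the only randomised comparison. The stated test instead asks whether any of three group means differ, and one of those groups was chosen for not having the disorder. A known or plausible difference between shift-work patients and healthy sleepers is enough to make it significant.

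The time point does not rescue it. At baseline the test shows disease differences. After treatment it mixes disease, needling and time. For change scores, both acupuncture groups may differ from untreated controls for reasons shared by true and sham needling.

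Two further gaps add to this. An undefined FDR family leaves the error rate of the primary claim open. And a connectivity difference with no stated beneficial direction cannot by itself establish a therapeutic effect. At stake is a trial reported as positive on its primary outcome with no evidence that true acupuncture differs from sham.

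**Working it through.** **The plan's own figure.** 60 + 30 = 90 participants; 90 / 3 = 30 per group. Section 2.6 justifies this by a literature range of 16 to 32, which contains 30. It gives no effect size, SD or power, so there is no power calculation to reproduce.

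**What the three-group test responds to.** Let true and sham be identical, each shifted from healthy controls by d standard deviations (assumed). The means are 0, d, d, with average 2d/3. The noncentrality of the F test on 2 and 87 degrees of freedom is

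λ = 30 × (4d²/9 + d²/9 + d²/9) = 20d².

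- d = 0.5: λ = 5, and the test is significant at 0.05 with probability 0.49.
- d = 0.8: λ = 12.8, and the probability is 0.89.

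That is for one connection, with no difference at all between true and sham.

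**The same with FDR over many connections.** Simulation with 30 per group, independent connections, Benjamini-Hochberg at 0.05, TATG = SATG throughout; 2,000 runs for 45 connections (10 components, assumed: 10 × 9 / 2) and 600 runs for 435.

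| Connections | Shifted versus controls | d | Any significant, three-group ANOVA | Any significant, TATG vs SATG |
|---|---|---|---|---|
| 45 | 0 | – | 5.8% | 4.9% |
| 45 | 1 | 0.5 | 14.5% | 5.4% |
| 45 | 1 | 0.8 | 50.9% | 5.9% |
| 45 | 5 | 0.5 | 39.8% | 4.6% |
| 45 | 5 | 0.8 | 97.0% | 5.0% |
| 435 | 0 | – | 5.2% | 5.2% |
| 435 | 20 | 0.5 | 44.5% | 4.3% |
| 435 | 20 | 0.8 | 99.8% | 6.0% |

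The ANOVA is doing its job: it detects the patient–control difference. It does not address the treatment question.

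**The FDR family.** The rows with no shift show that FDR holds the chance of any finding near 5% within one family. For m independent families each at 5%, the chance of at least one is 1 − 0.95^m:

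- m = 2 (intra, inter): 1 − 0.9025 = 9.8%.
- m = 4 (each at two time points): 18.5%.
- m = 12 (each also for three pairwise contrasts): 46.0%.

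These are illustrations. The article does not say how many families there are, and correlated families would give lower values.

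**Size of the outcome.** All 30 components would give 30 × 29 / 2 = 435 pairs plus 30 maps. That is an upper bound, because components are discarded. Keeping 7 to 14 (assumed) leaves 21 to 91 pairs.

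**After the change.** With one named measure, TATG versus SATG, two-sided 0.05 and 30 per arm, the difference detectable with 80% power is (1.960 + 0.842) × √(2/30) = 0.72 SD. Power is 49% at d = 0.5 and 87% at d = 0.8.

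**The case against.** A full protocol or analysis plan may list the networks, templates, time point and pairwise tests, and an article need not. That is fair for templates and network lists, whose absence is not held against the plan. It does not cover the test. Section 5.2.2 commits to software, component count, test and threshold, and the test it commits to is not a treatment contrast.

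A reader might also infer four stronger faults, which the article does not support.

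- *A false-positive rate far above 5%.* This needs FDR to be applied separately to many analyses. With 31 independent families, for instance, 1 − 0.95^31 is 80%. The article does not say the correction is separate, and non-network components are dropped before testing. What stands is that the family is undefined.
- *Components chosen to suit the result.* Selection is by spatial match to existing templates, and section 2.7 blinds the data analysts.
- *A contradiction between "The number of independent components in all data was calculated by method of the minimum description length (MDL) technique" and "30 components were estimated".* The two can be read as MDL returning 30, and the article uses the past tense for planned work elsewhere. Reporting an estimate before scanning is odd, but no more.
- *No outcome in the trial can show benefit.* RBANS, ANT and PSQI are collected, and the therapeutic aim refers to the study's results as a whole. The limit applies to connectivity taken alone.

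The sentence beginning "The best goodness-of-fit score of components were normalized to" is also unclear. A fit score is one number per component, and Fisher's transformation is meant for correlations. It may simply mean that the best-fitting component's map was standardised, so this is a minor correction.

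**Conclusion.** The point holds. The primary outcome is a class of measurements tested by a three-group ANOVA with no time point, randomised contrast or FDR family fixed. Followed as written, it can be positive when true and sham acupuncture do not differ: in 40% to 97% of simulated runs with 5 of 45 connections shifted by 0.5 to 0.8 SD, against about 5% for true versus sham. Those percentages rest on assumed effect sizes, connection counts and independence. The conclusion does not; it needs only that patients and healthy controls differ somewhere.

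The family question is smaller and uncertain: about 5% under the global null if there is one family, about 9.8% for two independent ones, more for more. A connectivity difference without a stated beneficial direction supports a statement about mechanism, not a therapeutic claim.

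**What to change.** Before group codes are opened:

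1. Make the primary analysis the TATG-versus-SATG comparison of post-treatment connectivity adjusted for baseline (or of change). Use healthy controls only as a descriptive reference.
2. Apply one FDR correction across all retained intra- and inter-network tests. Alternatively, name one primary measure and put the rest in one secondary FDR family.
3. Rest any therapeutic claim on a named clinical endpoint already collected, for example RBANS total, TATG versus SATG. Describe connectivity findings as mechanistic.
4. Minor: state that component maps are scaled to z, and keep Fisher's r-to-z for network-pair correlations.

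No new patients, scans or tests are needed. The cost is that the outcome wording in the protocol must be amended, not only the analysis text, and connectivity findings outside the primary contrast or measure become secondary or exploratory.

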### Cognitive function assessments and outcomes

4.3

The following cognitive function assessment scales, including Repeatable Battery for the Assessment of Neuropsychological Status (RBANS) and Attention Network Test (ANT), will be conducted at the baseline and after the 4-week acupuncture treatment by a trained assessor blinded to the random sequence. The results of RBANS and ANT will be taken as the secondary outcome in this trial.

#### Repeatable Battery for the Assessment of Neuropsychological Status (RBANS)

4.3.1

RBANS, a cognitive screening test including 12 subtests, was utilized as the measure of global cognition. The RBANS generates 5 domain-specific index scores applied to evaluate 5 cognitive abilities: immediate and delayed memory, language, visuospatial/constructional ability and attention. In spite of delayed memory, a component based on 4 subtests, the other 4 are based on 2 subtests. The immediate memory index comprises the story memory and list learning subtests; the visuospatial/constructional index comprises the line orientation and figure copy subtests; the language index comprises of the photo naming and semantic fluency subtests. The attention index comprises the digit span and coding subtests; the delayed memory index comprises the list recall, story recall, list recognition and figure recall subtests. The Chinese version of the RBANS translated by Cheng et al was adopted in the current study.^[25]^ The test undergoes about 30 minutes. A trained neuropsychologist performed the test according to standardized procedures.

#### Attention Network Test (ANT)

4.3.2

ANT, a cognitive task designed by Fan et al,^[26]^ was used to evaluate the efficiency of the alerting, orienting, and executive control. Subjects were required to click the mouse as quickly and accurately as possible to define the direction of the target, which was a rightward or leftward arrow in the center of screen and flanked on either side by 2 arrows in the same direction (congruent condition), or the opposite direction (incongruent condition). Each subject performed 6 blocks during this test, while each block last 5 minutes 42 seconds and included 36 trials plus 2 buffer trials. During each block, the 6 trial types were displayed in a predetermined counterbalanced order. All participants would be trained before the formal test. The entire test would be conducted on an experimental control computer.

### Pittsburgh Sleep Quality Index scale (PSQI)

4.4

Pittsburgh Sleep Quality Index (PSQI), was used to evaluate the quality of sleep.^[27]^ This scale could measure the quality and patterns of sleep during the last 1 month. It included 7 domains: subjective sleep quality, use of sleep medication, sleep latency, sleep duration, habitual sleep efficiency, sleep disturbances and daytime dysfunction. Each items varied from 0 to 3 scale. An overall score of 5 or greater indicates poor sleep.

### Needle sensation assessment

4.5

The needle sensation assessment scale will be conducted after each acupuncture treatment by the acupuncturists. The result may be a prognostic marker associated with the effectiveness of acupuncture and improvements of cognitive function, which will be taken as the additional outcomes.

“*Deqi*” is a needle response describing how the patients feel when they receive the needle insertion. The self-designed Needle Sensation Assessment Scale has been applied in previous studies,^[28]^ including “*Deqi*” features (tingling, numbness, sourness, aching and propagated feeling along the meridians) and rating of “*Deqi*”. Patients will describe the intensity of needle sensation by visual analogue scale (VAS) (0 stands for none, 10 stands for unbearable).

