## Discussion

6

Acupuncture is a common therapy for insomnia in China, and great progress has been made in the study of its pathogenesis.^[29]^ Systematic reviews and a large number of trials have confirmed that acupuncture is safe and effective in the treatment of insomnia.^[30,31]^ However, there are few studies on acupuncture treatment of SWD. Previous studies and literatures have shown that acupuncture can effectively treat insomnia and sleepiness of shift work disorder, and improve attention decline.^[32]^ In the current research, we will focus on the effect of acupuncture on cognitive functions of patients with SWD, and explore the neural mechanism of acupuncture on SWD through fMRI.

A large number of studies showed that, the activity of cerebral cortex and the internal and external functional connectivity of neural network were closely related to the occurrence of shift work disorder.^[33,34]^ Meanwhile, the fMRI technology provides a direct tool for the study of brain response to acupuncture intervention. Numerous studies revealed changes of the brain's intrinsic functional connectivity stemming from cognitive impairments on patients with sleep disorder.^[23,24]^ A previous study also reported that patients with SWD showed brain perfusion changes in multiple brain areas significantly correlated with insomnia severity.^[35]^ In this study, the relationship between acupuncture sensation and fMRI is preliminarily discussed. fMRI can infer that regional changes in brain activity reflect whether specific brain regions or resting-state brain networks are involved in improvements of cognitive functions after 4-week acupuncture treatments.

However, there are few studies on acupuncture in the treatment of SWD, which need to be further studied through larger, more rigorous and good randomized clinical trials. At the same time, the purpose of setting up the false acupuncture group in this study is to eliminate the placebo effect. However, it is difficult for Chinese patients to choose the sham acupoint as the acupuncture placebo. As patients may have their own acupuncture treatment experience and know the location of common acupoints. In hence, the blinding of patients in this study has a certain impact.

In conclusion, the purpose of this study is to evaluate effect of acupuncture on cognitive impairments of SWD and to interpret the neural mechanism of acupuncture on SWD through fMRI.

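### The statement that outcome assessors are blinded is untrue for needle sensation, which acupuncturists who know the allocation collect at every session

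*Protocol article*

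**What the plan says.** **Blinding.** The abstract describes a trial "with enrolled participants, outcome assessors, and data statisticians blinded". Section 2.1 (Study design) makes the same claim. Section 2.7 (Randomization and blinding) says: "The researchers and acupuncturists will know the allocation". It continues: "Meanwhile, the participants, outcome assessors and data analysts will be blinded". None of the three places exempts an outcome.

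**Who collects needle sensation.** Section 4.5: "The needle sensation assessment scale will be conducted after each acupuncture treatment by the acupuncturists". The patient gives the intensity on a 0 to 10 visual analogue scale.

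**Status of the outcome.** The abstract's list of secondary outcomes ends with "Pittsburgh Sleep Quality Index scale and needle sensation assessment scale". Section 4.5 describes the needle sensation result as one "which will be taken as the additional outcomes".

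**Intended use.** Section 4.5 sees the result as a possible prognostic marker for the effectiveness of acupuncture and for cognitive improvement. The Discussion adds that the study will look at how acupuncture sensation relates to fMRI.

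**Handling of deqi.** In 3.1, needles in the true arm stay in place for 20 minutes once deqi has been obtained. Section 3.2 says that deqi will not be given undue emphasis in the sham arm, and also that everything except point location matches the true arm.

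**The concern.** Needle sensation is subjective and is reported within minutes of treatment to the person who gave it. That person knows the arm and, on one reading of 3.2, has pursued the sensation in one arm and played it down in the other. The way the question is put, the prompts used and the patient's wish to give a suitable answer can all differ by arm without anyone intending it. Assessor blinding exists to prevent this, and the article claims it without exception.

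Two things are at stake. First, a reader of the eventual report would take the needle sensation data as collected blind, and they would not be. Second, the score is meant to explain other results. If it is shifted in one arm, any marker analysis or fMRI correlation that uses it takes on the shift.

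**Working it through.** The question is who is blinded, so the check is mainly a comparison of statements. The article gives no figure to reproduce.

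**Step 1: can the statements all be true?**

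| Statement | Source |
|---|---|
| Outcome assessors are blinded, no exception | Abstract; 2.1; 2.7 |
| Acupuncturists know the allocation | 2.7 |
| Acupuncturists conduct the needle sensation scale | 4.5 |
| Needle sensation is an outcome | Abstract (secondary); 4.5 (additional) |

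From the last three rows, at least one listed outcome has an unblinded assessor, which contradicts the first row. The secondary or additional label makes no difference to this. A fuller protocol could correct one of the statements but could not make all four true.

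**Step 2: how much data is involved?** There are 60 patients randomized to true or sham needling (2.6, 2.7) and 8 sessions each (2.1), with an assessment after every session: 60 × 8 = 480 planned assessments, all collected unblinded. Averaging a patient's eight scores reduces random error but leaves a systematic difference in elicitation where it was.

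**Step 3: which outcomes does the conflict not reach?** Section 4.3 gives RBANS and ANT to a trained assessor blinded to the random sequence. Functional connectivity, the primary outcome (4.2.2), is computed from scans, and 2.7 states that the data analysts are blinded. Section 4.4 names no assessor for the PSQI, so nothing there conflicts.

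**Step 4: how would a shift act on the planned use?** A constant shift in one arm drops out of a correlation computed within that arm. It stays in a correlation pooled over both arms: if the true arm's scores are raised and its connectivity also changes more, the pooled correlation is inflated. The article does not say which form is meant.

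**Step 5: illustration of size, on assumptions only.** The article gives no SD for the scale and no elicitation effect. Assume 30 per arm, no true difference between arms, a two-sided 5% t test, and one score per patient. With d = shift/SD, noncentrality d × √(30/2) and 58 degrees of freedom, the chance of a significant arm difference is:

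| Assumed shift (points) | SD 2 | SD 1.5 |
|---|---|---|
| 0.5 | 15.9% (d = 0.25) | 24.6% (d = 0.33) |
| 1.0 | 47.8% (d = 0.50) | 71.9% (d = 0.67) |

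The range, 16% to 72%, is wide because the inputs have no anchor in the document. It shows only that a modest shift could matter. It does not estimate the bias in this trial, and the finding does not depend on it.

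**The case against.** The strongest reply is that this is a minor measure and the rater is really the patient. Section 4.5 has her describe the intensity herself, so the acupuncturist administers the scale and does not score it. That limits the bias but does not remove it, because she answers her own operator straight after needling.

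It can also be said that the article specifies no true-versus-sham test of needle sensation. The three-group ANOVA in 5.1 cannot include it, since the controls receive no needles, and needling true and displaced points may produce different sensations in any case. This stands. A significant arm difference would not automatically be false, and the illustration in Step 5 carries no weight as an estimate. The marker and fMRI uses remain exposed.

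The text on deqi is ambiguous, as 3.2 also says that the two procedures match apart from location. So differential pursuit of deqi is a possible reading, not an established fact.

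A reader might go further and infer that blinding fails across the trial, or that patients will know their arm and any PSQI difference is uninterpretable. The article does not support either inference. Blinded assessment or analysis is stated for the other outcomes named in Step 3. On patients, the Discussion gives a reason for doubt: "As patients may have their own acupuncture treatment experience and know the location of common acupoints". That leaves patient blinding unverified, not shown to have failed. The article describes no treatment guess and no record of prior acupuncture, but a condensed article may leave both to the full protocol, so their absence is not a finding.

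**Conclusion.** The point holds for needle sensation only. The unqualified claim of blinded outcome assessment in the abstract, 2.1 and 2.7 is contradicted by 4.5 read with 2.7, for all 480 planned assessments of an outcome that the abstract calls secondary. This conclusion rests on the text alone and needs no numerical assumption.

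The consequence is a risk of elicitation bias in a subjective score that is to serve as a prognostic marker and be related to fMRI. How large that bias would be, and in which direction, the document does not allow one to say. The two statements on deqi in 3.2 add to the risk on one reading and should be reconciled.

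The primary outcome and the cognitive tests are not affected, except where a later analysis correlates them with the needle sensation score. The change is worth making because a stated safeguard does not apply to a listed outcome and correcting it costs little. The point does not threaten the trial's main comparison.

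**What to change.** 1. **Section 4.5.** Have the patient complete the whole scale, including the VAS, herself and out of the acupuncturist's sight. She seals the form, which carries no arm label, and it goes to data entry staff who are blind to allocation. Cost: a revised form and procedure, and a short self-completed form at each of up to 480 sessions. This removes elicitation by an unblinded person. It does not remove any difference in how deqi was handled during needling.
2. **If that is not feasible,** limit the blinding statements in the abstract, 2.1 and 2.7 so that they exclude needle sensation, and report its results as collected unblinded. Cost: wording only, but the bias remains.
3. **Outcome status.** Call needle sensation either secondary or additional, in both the abstract and 4.5.
4. **Section 3.2.** Reconcile the sentence on deqi in the sham arm with the sentence that the procedures are otherwise the same.
5. **Optional.** Because the Discussion itself doubts patient blinding, add a one-line treatment guess early in the course and report it by arm, descriptively. Do not stratify the efficacy comparison by a week-4 guess: that guess is made after randomization and can be influenced by improvement, so conditioning on it can introduce bias.
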